### Participant timeline {13}

A schematic diagram (Fig. 4) shows the time schedule of enrolment, intervention assessments, and visits for all participants. Participants will be followed with 4-monthly intervals for 2 years within the double-blind RCT.

**Fig. 4 Fig4:**
[figure not shown]
A schematic diagram of the time schedule of enrolment, intervention assessments, and visits for all participants

### Sample size {14}

Based on the results of the first 120 patients included in the longitudinal Leiden-CSA cohort and the observation that 35% of the patients with a positive MRI developed RA within 6 months of follow-up, and the assumption that treatment will result in a 50% reduction in RA development after 2 years, a sample size of 182 patients is needed to provide 80% power based on a two-sided *Z* test with pooled variance and a significance level of 0.05. Applying a 20% dropout rate results in a total sample size of 230 patients (115 per treatment arm). This dropout rate is calculated based on the data from spring 2018, when the dropout rate within the first study year was estimated at 14%. Similar sample sizes occur when calculating the time to DMARD-free status as an outcome, which is the co-primary endpoint. Based on our finding that 45% of CSA patients in the Leiden-CSA cohort had a positive MRI, we anticipate that we have to screen > 500 CSA patients to identify 230 patients with a positive MRI.

The sample size was determined for the primary endpoint. The sample size was not set to detect powered effects on the number of secondary endpoints that are assessed. The results from secondary endpoint analyses will be interpreted cautiously and in relation to the estimated confidence limits on the actual scale of the measurements. *P* value testing will be restricted, and results that are significant in isolation will be interpreted less strongly than the sets of results that are mutually supportive or that support the corresponding primary endpoint.

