The mechanisms underlying arthritis becoming chronic are poorly understood. The development of RA is considered to be a multiple-hit process that is largely taking place before the disease presents with clinically swollen joints. Different phases in the development of RA are described by a “European League Against Rheumatism” (EULAR) taskforce [5, 6]; the phase that precedes the development of clinically apparent arthritis is a phase of symptoms. The pattern of symptoms that characterizes this pre-arthritis phase has been called clinically suspect arthralgia (CSA) [7]. The clinical expertise (relying on pattern recognition) of rheumatologists has been shown accurately in the identification of patients with arthralgia at risk for RA among all patients with arthralgia presenting to secondary care (odds ratio 55, sensitivity 80%, specificity 93%) [8]. In this phase of CSA, patients have not only symptoms such as pain and stiffness but also functional limitations [9]. Sick leave and disability pensions are described to rise 6 months before the diagnosis [4]. Additionally, patients can have maturing auto-antibody response or increased levels of pro-inflammatory cytokines in the systemic circulation [10, 11]. Together, these findings illustrate the relevance of the CSA phase from the patients’ perspective and the immunological perspective.

Although clinical joint swelling is per definition absent in CSA, patients can have subclinical joint inflammation in the hands or feet, that is, synovitis, tenosynovitis, and/or inflammation of the subarticular bone, also called osteitis or bone marrow edema (BME). Magnetic resonance imaging (MRI) is a sensitive tool to detect subclinical joint inflammation. Furthermore, the definition of the presence of (“positivity for”) subclinical joint inflammation was established by the generation of a reference atlas from persons from the general population [12, 13]. Including information on MRI findings from age-matched symptom-free persons (same feature, same anatomic location), a highly specific definition was obtained without losing sensitivity. The presence of subclinical inflammation in patients with CSA is associated with a risk of 32% to progress to RA during the next year [14]; the NPV is 93%, indicating an acceptable ability to detect RA in a symptomatic pre-arthritis phase and a low chance to miss patients because of false-negative results.

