The primary endpoint can be considered as the main outcome assessed from the perspective of rheumatologists, but patients indicated that the burden of RA is best expressed by assessing the domains of independence (functioning, workability), pain, and fatigue [50]. The secondary endpoints may therefore be considered as the benefit from very early treatment from patients’ perspectives. Moreover, an evaluation 1 year after the cessation of study medication may be insufficient to determine if favorable effects are sustainable over time [49]. Thus, as PROs are considered most valuable by patients, and as the 2 years measurement insufficiently assesses sustainability, all secondary endpoints will also be analyzed again 5 years after the study start.

This trial was designed in 2014, and risk stratification was based on the first 120 included Leiden-CSA patients, which resulted in a risk of 35% to progress to RA during the next year (PPV) in patients with CSA and a positive MRI. Based on these numbers, a sample size of 230 participants was required for a well-powered study. Recently, it was observed that higher PPVs can be obtained when weighting tenosynovitis (particularly, MCP extensor peritendinitis) and the number of locations with subclinical inflammation (PPVs up to 63–67%) [17]. This creates opportunities for (subgroup) analyses on participants with high-risk characteristics.

CSA patients will be enrolled in this trial irrespective of the auto-antibody status as it has been reported that with current treatment strategies, the disease burden is similar in ACPA-positive and ACPA-negative RA patients [19], and in addition, EULAR recommendations for the management of early arthritis recommend MTX as the first-line therapy, independent of the auto-antibody status [20]. Nevertheless, there is accumulating evidence that ACPA-positive and ACPA-negative RA have different etiopathologies, as underlying genetic [51] and environmental risk factors differ [52, 53]. Also, subtle differences in symptoms [54] and timelines of the symptomatic phase that precedes the development of clinical arthritis have been reported [55]. It is therefore possible that disease maturation in the symptomatic pre-arthritis phase differs between the two groups. Consequently, the influence of treatment may be different in APCA-positive and ACPA-negative CSA. In addition to adding an adjustment factor, this can be addressed by stratifying the analyses for ACPA.

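### The 35% control risk carries two different time windows, neither of them 2 years; its stated inputs give about 77% power at 182 patients, not 80%; and the step from 14% to 20% dropout is not shown

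*Protocol article*

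**What the plan says.** All places are in the protocol article.

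- **Sample size {14}, control risk:** taken from the first 120 patients of the Leiden-CSA cohort, with "the observation that 35% of the patients with a positive MRI developed RA within 6 months of follow-up".
- **Sample size {14}, effect:** "the assumption that treatment will result in a 50% reduction in RA development after 2 years".
- **Sample size {14}, test:** 182 patients are said to be needed "to provide 80% power based on a two-sided" Z "test with pooled variance and a significance level of 0.05".
- **Sample size {14}, dropout:** a 20% allowance takes 182 to 230 (115 per arm). The allowance is said to be calculated from data of spring 2018, "when the dropout rate within the first study year was estimated at 14" percent.
- **Discussion:** the first 120 cohort patients supplied the basis, "which resulted in a risk of 35% to progress to RA during the next year (PPV) in patients with CSA and a positive MRI", and the 230 is said to follow from these numbers.
- **Outcomes {12}:** the primary endpoint is RA by the 2010 criteria or unclassified arthritis of at least 2 joints, persisting for at least 2 weeks, collected over 2 years.
- **Statistical methods {20a}:** the primary analysis is time to event, and the co-primary endpoint is tested only if the primary test is significant.

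**The concern.** Three things do not fit together.

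1. The same percentage, from the same patients and for the same purpose, is a 6-month risk in one section and a 1-year risk in another. At least one label is wrong. Neither window matches the 2 years at which the halving is assumed, and both figures count RA alone, whereas the endpoint is wider.
2. The stated number of patients does not follow from the stated rates, test, level and power.
3. An allowance covering 24 months is attributed to a 12-month observation, without the intermediate step.

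The stated 80% is what a reader will use to interpret a non-significant primary result. Such a result would also close the gate to the co-primary endpoint. The reader should be able to trace that 80% to a control rate, a horizon and a dropout figure, and at present cannot.

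**Working it through.** **Inputs.** Control risk p1 = 0.35; 50% reduction, so p2 = 0.175; two-sided alpha 0.05 (z = 1.960); power 80% (z = 0.842); pooled-variance Z test (all Sample size {14}); 1:1 allocation (Intervention description {11a}).

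**1. The plan's own figure.** With pbar = (0.35 + 0.175)/2 = 0.2625,

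n per arm = [1.960·√(2·pbar·(1−pbar)) + 0.842·√(p1(1−p1) + p2(1−p2))]² / (p1−p2)²

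- First term: 1.960 × 0.6222 = 1.2196
- Second term: 0.842 × 0.6098 = 0.5132
- n = (1.7328)² / 0.175² = 98.05, rounded up to 99 per arm, **198 in total**, against 182 stated

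Other methods with the same rates do not give 182 either: unpooled variance 192, arcsine 194, pooled variance under both hypotheses 200, continuity correction 220. A log-rank calculation (Schoenfeld) at the hazard ratio implied by 35% and 17.5%, 0.447, gives 187; it comes closest but is not the stated method. The stated test gives exactly 182 at 37% against 18.5%, a rate that the document does not mention.

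The dropout step does reproduce: 182/0.80 = 228, close to 230. Applied to 198 it gives 248.

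**2. Power at the stated size.** Power = Φ{[(p1−p2)·√n − 1.2196] / 0.6098}.

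- 91 per arm (182): (1.6694 − 1.2196)/0.6098 = 0.738, power **77.0%**
- 92 per arm (230 × 0.80 = 184): (1.6785 − 1.2196)/0.6098 = 0.753, power **77.4%**

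Exact binomial power of the same test is 77.5% and 78.1%, so the approximation does not explain the gap.

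**3. Dropout.** If 14% is lost in year 1, a 20% total implies 1 − 0.80/0.86 = 7% in year 2. The text does not give that figure. If 14% recurred in year 2 (assumption), the total is 1 − 0.86² = 26%. That leaves 230 × 0.86² = 170 evaluable, 85 per arm.

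**4. Control rate and dropout together.** The documents give no 2-year composite rate, so the rates above 35% are assumptions. Pooled Z test, 50% reduction throughout, 230 randomised:

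| 2-year control rate | 20% dropout (92 per arm) | 26% dropout (85 per arm) |
|---|---|---|
| 35% | 77% | 74% |
| 37% | 80.5% | 77% |
| 40% | 85% | 82% |

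**The case against.** The strongest reply is that the mismatch is conservative. For patients of the same risk, a 2-year cumulative rate cannot be below a 6-month or 1-year rate, and RA alone cannot be more frequent than RA or unclassified arthritis. Both features make 35% too low for the endpoint, and at a fixed 50% reduction a higher control rate raises power. A rise of only 2 points, to 37%, restores 80% at 92 per arm. This stands. A reader might infer from the short horizon that the trial is underpowered; the documents do not support that.

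The dropout figure is also open to challenge, and most of the challenge stands. The 20% exceeds the observed 14%, so some year-2 loss is already allowed for. Year 2 is off study medication, and participants who stop tablets are asked to stay in follow-up, so a constant rate may be too pessimistic. Counting dropouts as no information is harsher than the planned time-to-event analysis, particularly as the Discussion says that most conversions occur within 4 to 6 months. If all 230 contributed fully, power at 35% against 17.5% would be 86%. A reader should therefore take 26% as a bound and not as a forecast.

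A reader might also set the background's statement that subclinical inflammation "is associated with a risk of 32% to progress to RA during the next year" against the 35% and call it a third conflicting input. It is not one. It is cited background, is not said to come from the first 120 patients, and both sections that describe the calculation use 35%.

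None of this removes the two time windows for one figure, the missing step from 14% to 20%, or the fact that 182 does not follow from what is stated. These are printed in the article, so condensation or a separate analysis plan does not account for them.

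**Conclusion.** The point holds as an inconsistency in the sample-size basis and an overstated power figure. On the protocol's own inputs the shortfall is about 16 evaluable patients (198 against 182), or about 3 percentage points of power (77% against 80%). It arises because 182 does not reproduce, and not from the conflicting time windows.

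The conflicting windows and the unexplained dropout step leave the true power uncertain rather than low. Over control rates of 35% to 40% and dropout of 20% to 26%, power runs from about 74% to about 85%. That range assumes a 50% relative reduction throughout, the pooled Z test rather than the planned time-to-event analysis, and no information from dropouts. The stated 80% lies inside the range, but the text does not derive it.

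**What to change.** In the Sample size section, and in the Discussion where it repeats the basis:

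- Check the cohort data and give the 35% one time window in both places.
- State the control rate assumed at 2 years for the composite endpoint, and why.
- Show how 14% in the first year became 20% over 24 months.
- Correct either the 182 (about 198 at 35% against 17.5%) or the 80% (about 77% at 182 to 184 evaluable). If another control rate or method produced 182, name it.
- Report power for the 230 patients as a short range over control rates of 35% to 40% and dropout of 20% to 26%, roughly 74% to 85%.

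The cost is a rewritten paragraph and one look back at the cohort data. No additional patients are needed, and neither conduct nor analysis changes.

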### Intervention description {11a}

In this double-blind RCT, participants will be randomized to two arms in an 1:1 ratio. The randomization consists of one IM glucocorticoid injection (120 mg methylprednisolone or IM placebo injection) followed by 12 months of MTX tablets (or placebo tablets) (Fig. 2). No other corticosteroid interventions will be allowed during the trial, unless participants have reached the primary endpoint and proceeded to open-label DMARD therapy.

MTX (or placebo) tablets will be increased in 4 weeks to 10 tablets/week (25 mg/week). Open-label folic acid supplementation (5 mg/week) will be added, in line with the Dutch guidelines of MTX use (https://www.nvr.nl/richtlijnen/nvr-richtlijnen-standpunten-en-zorgpaden/). After 45 weeks of 10 tablets/week (MTX or placebo), tablets will be tapered for 4 weeks and then stopped at week 53. Participants will be followed for another 12 months.

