## Statistical methods

### Statistical methods for primary and secondary outcomes {20a}

All statistical methods for the primary and secondary endpoints will be described in the statistical analysis plan, which will be completed and submitted before unblinding. Analyses will be based on the intention-to-treat (ITT) and per-protocol (PP) population. The ITT population will consist of all participants randomly assigned to a treatment group. The ITT population will form the primary analysis population of the trial and will be used for all primary and secondary efficacy endpoints and for safety analyses. This strategy is conservative because it tends to underestimate the difference in the outcome between the treatment groups, but it respects the randomization process, is free from bias, and resembles clinical practice. The PP population will consist of all participants meeting the study entry criteria, who completed follow-up and who in the first year after randomization, or up to a primary event in this period, have used ≥ 8 study tablets a week (equivalent to at least 20 mg/week MTX) for 80% of the time and used no forbidden medication (no systemic or intra-articular steroids or DMARDs outside the study protocol) during the entire follow-up period. An MTX dose of ≥ 20 mg/week has been shown to provide optimal efficacy in RA [31, 32, 34]; therefore, a dose of ≥ 8 study tablets was incorporated in the definition. The PP population will consist of participants who strictly adhere to the protocol and provide an estimate of the true efficacy of the MTX intervention. All primary and secondary efficacy endpoints will also be analyzed in the PP population. The primary analysis will be the time to the development of the primary endpoint. The co-primary endpoint is the difference in the percentage of patients that achieved DMARD-free status at 24 months. Significance will be assessed by a gate-keeping analysis. We do prioritize the two primary endpoints by testing the primary endpoint first, and only if this test is significant, the co-primary endpoint will be tested.

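### The 182 patients said to give 80% power do not: the stated pooled Z test on 35% versus 17.5% needs about 198, and 182 to 184 give about 77%

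*Protocol article*

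**What the plan says.** The Sample size section ({14}) bases the calculation on the first 120 patients of the Leiden-CSA cohort, where "35% of the patients with a positive MRI developed RA within 6 months of follow-up", and on "the assumption that treatment will result in a 50% reduction in RA development after 2 years". From these it concludes that "a sample size of 182 patients is needed to provide 80% power based on a two-sided" comparison of the arms. The test is of the Z type: "test with pooled variance and a significance level of 0.05". The section then allows for losses: "Applying a 20% dropout rate results in a total sample size of 230 patients (115 per treatment arm"). Allocation is equal (Intervention description {11a}: "participants will be randomized to two arms in an 1:1 ratio").

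No other control rate, no absolute rate in the treated arm and no continuity correction is given for this calculation. The Discussion repeats the 35%, there as a risk over the next year, and says that on these numbers "a sample size of 230 participants was required for a well-powered study".

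Statistical methods {20a} specifies a different kind of analysis from the one used for sizing: "The primary analysis will be the time to the development of the primary endpoint", with all randomized participants as the primary population.

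**The concern.** The section names the test, its sidedness, the significance level, the power, one event rate and one relative effect. That is enough to recompute the sample size, and the result is not 182. The design therefore lacks the stated 80% power under the test it names. The target of 230 and the Discussion's statement about adequate power both rest on this figure.

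A second gap makes the first harder to pass over. The test used for sizing compares two proportions, while the planned primary analysis is time to event. The printed power is wrong for the named test, and none is printed for the analysis that will be run. A reader who later interprets a null or borderline result has no reliable figure for what the trial could detect.

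**Working it through.** **Inputs**

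- Control rate p1 = 0.35 (Sample size {14}).
- Treated rate p2 = 0.35 × 0.5 = 0.175. This is derived from the 50% reduction and is not printed.
- Two-sided alpha 0.05 (z = 1.960) and power 80% (z = 0.8416), from Sample size {14}.
- 1:1 allocation (Intervention description {11a}); 20% dropout (Sample size {14}).

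**Sample size with the named test**

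Mean rate = (0.35 + 0.175)/2 = 0.2625.

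n per arm = [1.960·√(2·0.2625·0.7375) + 0.8416·√(0.35·0.65 + 0.175·0.825)]² / 0.175²

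= [1.2196 + 0.5132]² / 0.030625 = 98.05

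This rounds up to 99 per arm, or 198 in total. The plan says 182, which is 16 fewer.

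**Power at the plan's own numbers**

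Power = Φ{[√n·0.175 − 1.2196] / √(0.35·0.65 + 0.175·0.825)}, with denominator 0.6098.

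| Evaluable per arm | Total | Power, pooled formula | Exact binomial power, same test |
|---|---|---|---|
| 91 | 182 | 77.0% | 77.5% |
| 92 (115 × 0.8) | 184 | 77.4% | 78.1% |
| 99 | 198 | 80.4% | 81.2% |
| 115 (no losses) | 230 | 85.9% | not computed |

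**Dropout step**

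182/0.8 = 227.5 and 184/0.8 = 230, so the inflation to 230 is consistent with rounding. The discrepancy is in the base figure. Starting from 198, the same step gives 198/0.8 = 247.5, so 248.

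**Could another version of the calculation give 182?**

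Two-sided variants with the same inputs:

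| Variant | Total |
|---|---|
| Unpooled variance | 192 |
| Arcsine | 194 |
| Pooled variance under both hypotheses | 200 |
| With continuity correction | 220 |

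All exceed 182 by at least 10. Results at or near 182 need something the text does not state:

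- 37% versus 18.5%: 90.8 per arm, total 182.
- 35% versus 16.9%: 90.9 per arm, total 182. With 17% it is 92.03 per arm, so 184 to 186 depending on rounding.
- One-sided with continuity correction: 178, but the text says two-sided.
- Log-rank (Schoenfeld): HR = ln(0.825)/ln(0.65) = 0.447; events = 4·(1.960 + 0.8416)²/(ln 0.447)² = 48.3; patients = 48.3/0.2625 = 184, or 49/0.2625 = 187 with events rounded up. The text names a Z test.

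**Power of the planned kind of analysis**

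Log-rank simulation assumed 230 randomized, 35% versus 17.5% at 2 years, and 20% dropping out evenly over the 2 years and censored at that point. Power was about 84% with a constant hazard and 85% with events concentrated early. The range over the simulations run was 83 to 85%.

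**The case against.** The strongest reply is that the 35% need not be the 2-year placebo rate. The section gives it as a cohort observation at 6 months, whereas the assumed effect is a reduction after 2 years. A 2-year placebo rate of 37% with the same test, alpha, power and 50% reduction gives exactly 182. A treated rate of 16.9% does too, so rounding of an unprinted input cannot be excluded. This stands as a possible origin of the figure. It does not make the printed statement correct: the text gives no such rate, and the Discussion ties the 230 to the 35%. Nor do the document's own figures point upward. The Background gives 32% at one year, and 32% versus 16% would need 222 evaluable patients.

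The second reply is that the consequence is small, and this largely stands. The 77% discards every dropout, but a time-to-event analysis of all randomized patients uses their follow-up until censoring. Under that analysis and the same effect, power is about 83 to 85%. At the 14% first-year dropout that the section reports, 230 × 0.86 = 197.8, so about 198 patients remain and the Z test itself has about 80% power.

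The third reply is that sizing a time-to-event trial from cumulative proportions is common practice. That is fair, and the mismatch alone would be a minor point. It matters here because the proportion-based figure is itself wrong, so the text contains no correct power statement.

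**Conclusion.** The concern holds. With 35% versus 17.5%, two-sided 0.05, 1:1 allocation and a pooled Z test, 80% power needs about 198 evaluable patients. The stated 182 gives 77.0%, and the 184 expected from 230 after 20% dropout give 77.4%. The shortfall is 16 evaluable patients, or 18 randomized (248 against 230), and about 3 percentage points of power.

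This rests on reading the 35% as the control rate and the 50% as a relative reduction applied to it, which is the only reading the printed inputs support. It does not show that the trial is underpowered for its primary analysis. If the assumed rates hold at 2 years and dropouts are censored, the power there is probably above 80%.

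**What to change.** Rewrite the paragraph in Sample size {14} in one of three ways:

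1. If 182 came from inputs not printed, state them: the 2-year placebo rate, the treated rate, and any rounding.
2. If 35% and 17.5% are the intended rates and the pooled Z test is kept, report about 77% power for 184 evaluable patients, and give 198 as the number for 80%.
3. Preferably, replace the calculation with one for the planned time-to-event analysis: assumed 2-year rates, implied hazard ratio, expected events, how dropouts are censored, and the resulting power with 230 randomized.

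Align the Discussion's sentence on power with whichever is chosen.

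The cost is one reworded paragraph and one sentence. No endpoint, analysis population, significance level or enrolment number changes. Under option 2 the stated power falls by about 3 percentage points. Under option 3 it would probably rise above 80%.

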### Methods: outcomes {12}

The key primary endpoint is the development of clinically detectable arthritis, either fulfilling the 2010 criteria for RA [22] or unclassified clinical arthritis with SJC-66 of ≥ 2 joints, which persists for at least 2 weeks. This primary endpoint (incidence) will be obtained during a 2-year follow-up.

The presence of clinical arthritis (swollen joints) is based on the physical evaluation of the joints by rheumatologists. In case of doubt on the presence of arthritis, it will not be scored. At the start of the trial, all treating rheumatologists attended a session to verify the comparability of determining the endpoint. They demonstrated to have a high interindividual agreement in the evaluation of the presence or absence of clinical arthritis at the patient level. The primary endpoint is not influenced by results from imaging. Ultrasound will not be done. MRIs made during the trial will be stored under a randomization number, and the results will not be reported back to participants or rheumatologists. Thus, also the MRI results are not included in the decision making on the clinical endpoint.

The co-primary endpoint is DMARD-free status. This is assessed at the 2-year follow-up time point and is defined as the absence of clinically detectable synovitis at the joint examination in the absence of DMARD use (including systemic or intra-articular glucocorticoids).

A key secondary endpoint is functioning (Health Assessment Questionnaire Disability Index (HAQ-DI) range 0–3); this will be assessed together with other patient-reported outcomes (PROs) that are interrelated but for which no composite measure exists:
Work productivity and impairment scale (WPAI) (per item percentage/number and numeric rating scale (NRS) range 0–10).Symptoms: pain (NRS range 0–10), fatigue (NRS range 0–10), and morning stiffness (NRS range 0–10, duration in minutes).

Explorative endpoints:

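### The sample-size section sizes the co-primary as a time to DMARD-free status, but the plan tests a month-24 percentage behind a gate; on the plan's own rates that test has about 77% power (75–76% gated), not 80%

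*Protocol article*

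**What the plan says.** Sample size {14} takes its control rate from a cohort finding: "35% of the patients with a positive MRI developed RA within 6 months of follow-up". For the effect it supposes that the intervention halves this rate by 2 years, i.e. 35% vs 17.5%. It concludes that "a sample size of 182 patients is needed to provide 80% power" with a two-sided pooled-variance Z test at 0.05, and inflates this for 20% dropout to 230 (115 per arm). On the co-primary it says only: "Similar sample sizes occur when calculating the time to DMARD-free status as an outcome, which is the co-primary endpoint". It gives no rate, effect size or number for that endpoint. The same section states that the size was determined for the primary endpoint.

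Methods: outcomes {12} makes the co-primary a status at the 2-year time point, "defined as the absence of clinically detectable synovitis at the joint examination in the absence of DMARD use". Statistical methods {20a} analyses it as a percentage: "The co-primary endpoint is the difference in the percentage of patients that achieved DMARD-free status at 24 months". The two endpoints are ordered "by testing the primary endpoint first, and only if this test is significant, the co-primary endpoint will be tested". The primary analysis is time to event.

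**The concern.** The sizing sentence describes a time-to-event outcome; the endpoint as defined and tested is a proportion at one visit. A statement about the first does not establish power for the second. The test can also lead to a claim only after a significant primary, so the chance of a co-primary claim is the probability that both tests succeed, which cannot exceed either one alone.

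The two endpoints need not carry the same contrast. A patient who developed arthritis but is free of swelling and DMARDs at month 24 passes the co-primary. A patient with one swollen joint that day fails it without necessarily meeting the primary definition, where unclassified arthritis needs at least two joints and all arthritis must persist for 2 weeks.

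What is at stake is interpretation. Persistence of disease is the trial's central hypothesis, and a reader told that similar numbers suffice would take a non-significant co-primary as coming from a test with 80% power.

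**Working it through.** **Inputs.** From Sample size {14}: 35% control, 17.5% treated (50% reduction), two-sided pooled Z, alpha 0.05, 80% power, 230 randomised, 20% dropout, 14% estimated first-year dropout. From Intervention description {11a}: 1:1 allocation. The co-primary has no stated rates, so the base case assumes that its failures equal the primary events.

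**The plan's own figure.** With mean rate 0.2625:

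n per arm = [1.960·√(2·0.2625·0.7375) + 0.8416·√(0.35·0.65 + 0.175·0.825)]² / 0.175² = (1.2196 + 0.5132)² / 0.030625 = 98.04.

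That is 196 in total unrounded, or 198 with 99 per arm. The stated 182 does not reproduce; the stated test gives 182 for about 37% vs 18.5%. The dropout step does reproduce: 182/0.8 = 227.5, taken up to 230. Starting from 198, it would be 198/0.8 = 247.5, i.e. 248.

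**Marginal power at month 24.** Power = Φ{[0.175·√n − 1.2196] / 0.6098}.

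- 20% loss: 230 × 0.8 = 184, 92 per arm. (1.6785 − 1.2196)/0.6098 = 0.753, so 77.4%. At 91 per arm (the stated 182) it is 77.0%.
- 14% loss: 230 × 0.86 = 197.8, about 98.9 per arm, so 80.3%.

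**Power through the gate.** This was simulated with 4,000 trials per setting and 115 per arm: log-rank test for the primary with 4-monthly detection and dropouts censored, then a pooled Z test on month-24 status in those not lost. Event timing, dropout pattern and the exclusion of dropouts are assumptions.

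| Scenario | Primary | Co-primary marginal | Both |
|---|---|---|---|
| Mirror, 20% loss | 82.4% | 78.0% | 75.5% |
| Mirror, 14% loss | 83.6% | 80.4% | 78.4% |
| 10% of converters DMARD-free | 83.6% | 72.7% | 70.1% |
| 5% of non-converters fail | 82.1% | 69.1% | 66.8% |
| Both departures | 83.2% | 63.8% | 62.0% |

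The last three rows use 20% loss and apply the departure equally to both arms. A second simulation with constant hazards gave 75% gated in the mirror case and 69%, 69% and 60% for the three departures. With events concentrated in the first 6 months it gave 77%, 70%, 68% and 60%.

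**Splitting the gap in the mirror case.** From 80% to about 77% is the 182 figure; from there to 75–76% is the gate, about 2 points.

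**Departures that favour treatment.** If 10% of control and 20% of treated converters are DMARD-free, the rates are 0.35 × 0.90 = 31.5% and 0.175 × 0.80 = 14.0%; at 92 per arm the marginal power is 81%. If 5% of control and 2.5% of treated non-converters fail, the rates are 38.25% and 19.56%, and the power is 80%.

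**The case against.** The strongest reply is that the sentence makes a marginal claim, and with equal rates both endpoints need the same number, so similarity is unsupported rather than refuted. The section already says that the trial was sized for the primary endpoint, and an article may leave co-primary inputs to the full protocol. That stands in part: the missing inputs alone would not be a finding. The mismatch between a time to status and a month-24 percentage is, however, in the article's own text, and so is the 182 that its stated test does not give.

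Three stronger readings are tempting and do not hold.

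- A reader might take 75–77% as a ceiling. It is not. At 14% loss power is about 80% marginal and 78–79% gated. At 40% vs 20% with 20% loss it is about 85% and 83%. The latter is not excluded, because Sample size {14} attaches the 35% to 6 months and the Discussion to the next year, so the 24-month control rate could be higher.
- A reader might blame the gate. It costs about 2 points when the endpoints nearly coincide.
- A reader might infer that a significant primary with a non-significant co-primary is likely under the planned effect. In the mirror case its probability is 82.4% − 75.5% = about 7%. It reaches 13–15% with one assumed departure and about 21% (83.2% − 62.0%) with both.

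The departures are also assumed in one direction. The trial's hypothesis of disease modification could make treated converters DMARD-free more often than controls, which keeps power at about 80%.

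**Conclusion.** The point holds in limited form. The sizing statement refers to an outcome that is not the one tested, and the 80% it implies is not reached on the plan's own rates and dropout: about 77% marginal and 75–76% gated, assuming that the co-primary mirrors the primary and that patients lost are not analysed at month 24. Most of the gap is the 182, which should be 196–198 under the stated Z test. That error affects the primary's stated calculation equally, although the planned time-to-event analysis has about 82% power in the simulations.

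The range of about 60–70% gated power is a sensitivity result. It requires 10% of converters DMARD-free and/or 5% of non-converters failing at month 24, equally in both arms, and the document gives no rates that confirm or exclude this.

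**What to change.** In Sample size {14}:

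1. Replace the sentence on time to DMARD-free status with the comparison actually planned: the percentage DMARD-free at month 24, tested only after a significant primary.
2. State the assumed DMARD-free percentage in each arm, with marginal and gated power at 230 randomised. Under the plan's own rates and 20% loss these are about 77% and 75–76%. Label any departures from the primary contrast as sensitivity assumptions.
3. Correct 182 to 196–198 evaluable, or keep 182 and restate its power as about 77% under the stated Z test.

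This needs a change of text only and no extra patients. The cost is a slightly less favourable stated power.
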